**Figure 2 F2:**
[figure not shown]
Participant flow. IAD, incontinence‐associated dermatitis; MDS, Minimum Data Set.

### Sequence allocation, randomisation, allocation concealment and blinding

A computer-generated randomisation sequence with 1:1 allocation to either implement the IAD care manual or usual care (control) to prevent and treat IAD will be used. The sites will be stratified to ensure balance between arms in home care agency and care homes (one home care agency and two care homes in each arm). Staff at the six study sites cannot be blinded as they will know whether they are using the IAD manual or providing usual care to prevent and treat IAD. Participants will be blinded as they will not know whether they are receiving care from the IAD manual. Care staff will be asked not to disclose the use of the manual to the participants whom they treat. The trial statistician will not be blinded, but the senior statistician will remain blinded throughout the study. The research team members who are consenting, delivering the training and conducting data collection will be unblinded. All other research team members will remain blind to the allocation.

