## Methods and analysis

### Trial design and setting

A two-arm feasibility cluster randomised controlled trial (RCT) will be conducted for 6 months. It will take place in four care homes (two in region A and two in region B) and two home care agencies (one in region A and one in region B). Region A comprises the largely urban setting of London, UK and region B denotes a more rural area and relatively smaller cities of Hampshire, UK. The term, care home, describes both nursing and residential care homes where people live to receive support with personal and social care. Home care agencies are professional organisations that provide personal and social care to adults living in their own homes. These are settings and services most likely to provide care to people with incontinence.

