### Sample size

Two care agencies and four large care homes each with approximately 100 residential and nursing care beds will be recruited and randomised as a cluster (one home care agency and two care homes in region A, with equivalents in region B). An IAD prevalence of 30% would provide 180 people with IAD (from 600) and would be sufficient to estimate recruitment and retention rates (80% recruitment, n=144) with a maximum margin of error of approximately ±7%. Forty-eight individual participants with incontinence (with or without IAD) will be recruited per site, anticipating a mean of 58 people with incontinence per 100 beds, and 30 with IAD per 100 beds.^7 12^ An overview of the planned participant flow is shown in figure 2.

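### Sites are stratified by setting but not by region, so 1 in 3 allocations splits the care homes entirely by region, and half of those make arm and region identical

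*Protocol article*

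**What the plan says.** The section on sequence allocation and randomisation in the protocol article sets 1:1 allocation and names one balancing factor, the type of care setting: "The sites will be stratified to ensure balance between arms in home care agency and care homes". It states the result this is meant to guarantee: "one home care agency and two care homes in each arm".

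Region is built into site selection but not into allocation. Trial design and setting says: "It will take place in four care homes (two in region A and two in region B) and two home care agencies", with one agency per region. Sample size repeats the layout: "one home care agency and two care homes in region A, with equivalents in region B". The two regions are presented as different in kind: region A is largely urban London, while "region B denotes a more rural area and relatively smaller cities of Hampshire, UK".

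The article does not say that allocation is stratified, paired or otherwise restricted by region.

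**The concern.** With six clusters and two regions of three sites each, balancing on setting alone still allows allocations in which region and arm coincide, wholly or for the care homes.

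The article gives reasons to think region could matter. It contrasts urban with more rural settings. The Discussion notes that staff turnover is often high in metropolitan areas, which bears on training, adherence and the weekly data that staff complete. Recruitment in region B has its own lead, and each region's university holds identifiable data.

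Two uses of the data are exposed:

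- **Arm contrasts.** Objectives makes retention and attrition in each arm a primary objective. Pilot outcome analysis uses signs of a difference between arms to help choose outcomes for the definitive trial.
- **Regional spread of experience with the manual.** Under Process outcomes and Process evaluation, acceptability of the intervention is explored at the three intervention sites, and adherence to the manual can be shown only where the manual is used. If those sites cluster in one region, the other region contributes little or nothing on delivery.

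**Working it through.** **Inputs**

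- Care homes: two in region A (A1, A2) and two in region B (B1, B2). Source: Trial design and setting.
- Agencies: one in each region (GA, GB). Same source, repeated in Sample size.
- Allocation 1:1, stratified by setting only. Source: the randomisation section.
- Assumption: within each stratum, all allocations are equally likely.

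**Step 1. The plan's own arm composition.** 4 homes / 2 arms = 2 per arm, and 2 agencies / 2 arms = 1 per arm. This reproduces the stated composition. The article gives no probability of regional imbalance to reproduce.

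**Step 2. Number of allocations.** C(4,2) × C(2,1) = 6 × 2 = 12.

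**Step 3. Enumeration by the region of the intervention sites.**

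| Intervention homes | Ways | Intervention agency | Allocations | Intervention sites in A |
|---|---|---|---|---|
| A1, A2 | 1 | GA | 1 | 3 |
| A1, A2 | 1 | GB | 1 | 2 |
| one A, one B | 4 | GA | 4 | 2 |
| one A, one B | 4 | GB | 4 | 1 |
| B1, B2 | 1 | GA | 1 | 1 |
| B1, B2 | 1 | GB | 1 | 0 |

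- Both intervention homes in one region, hence both control homes in the other: 1 + 1 + 1 + 1 = 4 of 12 = 1/3.
- All three intervention sites in one region, so arm equals region: 1 + 1 = 2 of 12 = 1/6. These two lie inside the four above.
- Remaining 4 − 2 = 2 of 12 = 1/6: the intervention homes share a region and the intervention agency is in the other.
- Intervention sites in region A number 0, 1, 2 or 3 with probability 1/12, 5/12, 5/12 and 1/12.

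**Step 4. Comparison with no stratification.** Choosing 3 of 6 sites freely gives C(6,3) = 20 allocations, of which 2 are fully confounded: 2/20 = 1/10. Stratifying on setting alone therefore raises the chance of complete confounding from 1/10 to 1/6.

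**Step 5. Homes randomised within region.** 2 (region A homes) × 2 (region B homes) × 2 (agencies) = 8 allocations. Each arm always has one home from each region, so both events have probability 0. The intervention arm has either two sites in A and one in B or the reverse, with probability 1/2 each. An even regional split is impossible with three sites per arm.

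**Step 6. The agencies.** There is one per region and one per arm, so the agency comparison coincides with region in all 12 allocations, and in all 8 after the change.

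**The case against.** The best case for leaving the plan alone is that this is a small, descriptive feasibility trial.

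- **No testing, and thresholds that do not compare arms.** Data analysis rules out significance tests. The thresholds under Prevalence and incidence concern pre-intervention prevalence by site, the share screened and the share of outcome measures completed by staff. The fidelity threshold concerns adherence to the manual. This stands: none is an arm contrast, so confounding of arm with region does not undermine them.
- **Most allocations are acceptable.** In 10 of 12, both arms contain both regions, and in 8 of 12 the homes are already split as the proposed change would split them. This also stands. The harm is conditional on an unlucky draw.
- **Setting is a reasonable stratifier.** The Introduction gives different incontinence and IAD figures for community and nursing-home populations, and no outcome figure by region of England. The size of any regional effect is therefore unknown. But the change keeps the balance on setting, so nothing has to be traded for it.

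Two stronger readings are tempting and should not be drawn. A reader might infer that results by arm will be uninterpretable in general. That applies only to arm contrasts, and only under the confounded allocations; pooled and per-site rates remain usable throughout. Nor is acceptability of the intervention an arm comparison; its exposure is loss of regional spread.

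A reader might also take the Sample size wording, "will be recruited and randomised as a cluster (one home care agency and two care homes in region A, with equivalents in region B", to mean that each region's sites are allocated as one block. The Abstract counts six clusters and the randomisation section stratifies the sites. Two regional blocks would be two clusters with nothing left to stratify. The sentence is loose, but it is not evidence of allocation by region.

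**Conclusion.** The point holds as an avoidable weakness in the allocation scheme. There is a 1 in 3 chance that the care-home comparison coincides with region and, within that, a 1 in 6 chance that the whole arm comparison does. In the 1 in 6 case, neither by-arm retention and attrition nor the descriptive look for a difference can be separated from London versus Hampshire, and one region supplies no experience of delivering the manual. In the other half of the 1 in 3, the same confounding applies to the care homes, and one region supplies no experience of the manual from care homes.

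The probabilities are exact, given equally likely allocations within each setting and no regional constraint beyond what the article states. How much harm follows depends on how different the regions are, which the article does not quantify. Because the analysis is descriptive and the thresholds are not between-arm contrasts, this is an inexpensive design improvement worth making and does not threaten the trial's feasibility aims.

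**What to change.** In the randomisation section, state that the care homes are randomised within region, one per arm in each region, that the two agencies are randomised 1:1, and that all six sites are drawn together. The single draw stops the second home in a region from being predictable once the first is known. The stated composition of each arm is unchanged.

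The cost is a different randomisation list and 8 possible allocations in place of 12. The change is partial: the 2:1 or 1:2 regional split and the confounded agency comparison remain, and the article should say so.

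If the sites have already been allocated, report the realised region-by-arm layout and present by-arm outcomes by site. If the full protocol already restricts allocation by region, the article's randomisation sentence should be corrected to say so.

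Separately, reword the Sample size sentence so that it says each site is a cluster.

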#### Clinical outcomes

A member of the research team, who is a qualified health professional, will conduct a skin examination of the participants where moisture resulting from incontinence is likely to occur (buttocks region). This skin examination will determine the prevalence and severity of IAD indicated by the appearance of erythema, erosion, maceration and the presence of IAD pain. Participants will also be asked about their satisfaction with care and their mental health. These data will be collected at the start of the feasibility cluster RCT, at 3 months and at 6 months using the following outcome measures:

Ghent Global IAD Categorization Tool (GLOBIAD).^33^Minimum Data Set (MDS) for IAD.^2^Incontinence-Associated Dermatitis Intervention Tool (to enable assessment of darker skin tones).^34^Wong-Baker FACES Pain Rating Scale.^35^The Short Assessment Patient Satisfaction (SAPS).^36^Hospital Anxiety and Depression Scale (requested by PPI panel to include of assessment of psychological impacts of IAD)^37^

Care staff from all six study sites will also use the MDS for IAD to collect weekly data from the recruited adults living in care homes and their own homes. Therefore, the MDS will be completed on a single day concurrently but independently by a clinical member of the research team (at baseline, 3 months and 6 months) and the recruited care staff (weekly) across all study sites to assess the prevalence and severity of IAD if present. The quantitative data from these data collection tools will be collected using the online survey tool: https://www.onlinesurveys.ac.uk/, which is UK general data protection regulation (GDPR) compliant and certified to ISO 27001 standard. See onlinesupplemental files 3^ 4^.

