### Pilot outcome analysis

The analysis of GLOBIAD and MDS, Wong-Baker FACES Pain Rating Scale will estimate proportions of patients and 95% CI. The outcomes measured using the Incontinence-Associated Dermatitis Intervention Tool, the SAPS questionnaire, the Hospital Anxiety and Depression Scale will be presented as mean and SD for each treatment group. The analysis will be carried out on the trial population using an intention to treat analysis. Completeness of the data and indication of difference will be assessed to inform selection of feasible clinical outcomes for a definitive trial. There will be no imputation to deal with missing data.

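### Skin gradings are made by researchers who know the allocation, yet the arm difference in them may inform which outcomes go into the definitive trial

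*Protocol article*

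**What the plan says.** All places are in the protocol article.

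- **Blinding section** (sequence allocation, randomisation, allocation concealment and blinding): team members who are consenting, "delivering the training and conducting data collection will be unblinded". It adds: "All other research team members will remain blind to the allocation". Staff at the six sites cannot be blinded; participants are meant to be.
- **Clinical outcomes:** "A member of the research team, who is a qualified health professional, will conduct a skin examination of the participants". The purpose is to "determine the prevalence and severity of IAD indicated by the appearance of erythema, erosion, maceration and the presence of IAD pain". On timing: "These data will be collected at the start of the feasibility cluster RCT, at 3 months and at 6 months". The skin tools are GLOBIAD, the Minimum Data Set (MDS) and the IAD Intervention Tool. Care staff complete the MDS weekly, independently of the researcher.
- **Harms and safeguarding:** the research team shows intervention-site staff how to use the manual. **Process outcomes:** researchers observe skincare for adherence at 3 and 6 months.
- **Pilot outcome analysis:** "Completeness of the data and indication of difference will be assessed to inform selection of feasible clinical outcomes" for a definitive trial.
- **Data analysis:** results are descriptive, with no significance tests.

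**The concern.** The skin tools record what an examiner sees: redness, maceration, erosion. An examiner who knows that a site has the manual may resolve borderline skin in its favour without intending to. Keeping participants unaware does not protect a visual grading, and leaving out significance tests does not help, because this bias sits in the point estimate.

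In many feasibility trials this would matter little, because nothing is decided on the arm difference. Here the plan gives that difference a job: it informs which clinical outcomes go forward. The skin gradings could look more responsive than the measures participants report themselves (satisfaction, anxiety and depression) partly because of who graded them. Post-allocation incidence, which the Prevalence and incidence section intends for the definitive sample size, could carry the same bias.

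**Working it through.** The plan states no figure on this point, so there is none to reproduce. The check is a reading of the sections together, followed by an illustration of size.

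**Step 1. Is the grader unblinded?** Data collectors are unblinded (blinding section). The skin examination is data collection by a research team member (Clinical outcomes). So the grader knows the allocation. This follows directly from the text.

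**Step 2. Which time points are exposed?** Table 2 puts baseline before allocation. Weeks 12 and 24 come after it. Exposure is therefore mainly at weeks 12 and 24.

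**Step 3. Is there a blinded second rating?** The concurrent MDS is completed by care staff, who cannot be blinded. At intervention sites some of them have also been trained to identify IAD (Table 1, box 4). It is an independent rating but not a masked one.

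**Step 4. Are training, fidelity observation and grading kept apart?** No section says so, and none says that one person does all three.

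**Step 5. How large could a false difference be?** Suppose there is no true effect and a fraction d of IAD cases at intervention sites is graded as no IAD. The false difference is p × d.

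Inputs for p come from the Sample size section: 30 people with IAD per 100 beds, so 30%; and 30 with IAD among 58 with incontinence, so 30/58 = 51.7%. The second fits the trial population better, since every participant is incontinent. The values of d are assumptions.

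| p | d | Read as | False difference |
|---|---|---|---|
| 30% | 1 in 10 | 27.0% | 3.0 points |
| 30% | 1 in 5 | 24.0% | 6.0 points |
| 51.7% | 1 in 10 | 46.6% | 5.2 points |
| 51.7% | 1 in 5 | 41.4% | 10.3 points |

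**Step 6. A second model.** Observed prevalence = p × sensitivity + (1 − p) × (1 − specificity). Control-arm grading is set at 0.90/0.90 and p runs from 20% to 51.7%. All accuracy values are assumptions.

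- Intervention-arm grading at 0.85/0.92: false difference −2.6 to −3.6 points.
- At 0.80/0.95: −6.0 to −7.6 points.
- At 0.70/0.95: −8.0 to −12.8 points.

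Worked case, p = 30% and 0.80/0.95: control 0.30 × 0.90 + 0.70 × 0.10 = 0.340; intervention 0.30 × 0.80 + 0.70 × 0.05 = 0.275; difference −6.5 points.

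**Step 7. Scale against noise.** With 48 per site and three sites per arm there are 144 per arm. The 95% half-width of a difference is 1.96 × √(2p(1 − p)/144): 9.2 points at p = 20%, 10.6 at 30%, 11.5 at 51.7%. This ignores clustering, which would normally widen it. Most of the false differences above lie inside this band. The arm difference is therefore a weak guide to outcome choice even before bias is considered.

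**The case against.** The unblinding is disclosed, not concealed, and nothing in the article contradicts it. Primary objectives are recruitment, retention, acceptability and fidelity; clinical outcomes are secondary and descriptive. Role allocation within the team is detail that a condensed article may leave to the full protocol.

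Most of this stands, and it rules out four stronger readings that a reader might infer:

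- **That the same person trains a site and grades its skin.** The article lists the roles together but does not say one person holds them. It is possible, not stated.
- **That the outcome with the largest difference will be chosen.** The difference only informs selection, alongside completeness; there is no such rule. GLOBIAD, the MDS and the Intervention Tool also share an examiner, so a common expectation would not clearly favour one of them over another.
- **That the progression criteria are compromised.** None uses an arm difference in skin grade. The 10% prevalence threshold is measured before the intervention; the others concern screening, completion by staff and fidelity.
- **That exchanging examiners between regions would mask them.** There is one home care agency per region and one per arm, so knowing one agency's allocation reveals the other's. If both care homes in a region share an arm, the same holds for the homes. Posters and flyers, which stakeholders asked for, could also reveal the arm. A truly masked assessor may need staff the article does not show.

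The objection does not remove the central point: the plan gives a design role to a comparison that its own blinding arrangements leave open to assessor bias.

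**Conclusion.** The point holds in limited form. By the article's own text, skin grading at weeks 12 and 24 is unblinded, the second rating is unblinded too, and the arm difference in those gradings may inform outcome selection. Illustrative false differences are about 3 to 10 points under simple downgrading and about 3 to 13 under the sensitivity and specificity model. Both rest wholly on assumed error rates; the documents give no evidence on the actual bias or its direction. The feasibility thresholds and baseline prevalence are not affected. This is an inexpensive improvement to how the results are used, not a reason to doubt the trial's main feasibility conclusions.

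**What to change.** **Main change, in Pilot outcome analysis.** State that the between-arm difference in GLOBIAD, MDS and Intervention Tool gradings will not guide the choice of outcomes for the definitive trial. Base that choice on:

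- completeness;
- acceptability to participants and staff;
- baseline prevalence and variability;
- agreement between the concurrent researcher and care-staff MDS ratings, shown by arm because intervention-site staff receive IAD training.

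Continue to report arm differences descriptively, with unblinded assessment stated as a limitation.

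**Addition, where existing staffing allows.** Specify that whoever trains staff or observes fidelity at a site does not grade that site's skin at weeks 12 and 24. This lessens the conflict of roles; it should not be described as blinding.

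**Cost.** The main change is a short amendment to the text and gives up one informal input to outcome choice; the agreement figures use ratings already planned. The addition needs some rota work. The article does not give the number of clinical researchers, so whether it can be done at every site is unknown.

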### Data collection methods

#### Process outcomes

A record of recruitment and retention rates (cluster and individual), attrition and completion of data collection by staff will be completed by researchers. The logic model (figure 1) will be used to monitor intervention fidelity and provide insight into how the intervention did or did not work in practice, identify any unintended consequences and refine the design of the definitive trial. A list of key assumptions and uncertainties will be explored by non-participant observation for 15–30 hours per care home and home care agency (at different times from early morning to evening). The aim is to observe at least 50 skincare procedures at each site at 3 and 6 months to assess adherence to the IAD Manual in a process evaluation. The number of non-participant observations is based on a pragmatic decision as there is little guidance as to the number of observations required to capture a complex intervention.^32^ Qualitative data from the observations will be collected at 3 months and then at 6 months during the feasibility study by the researchers.

Acceptability of the intervention at the three intervention study sites and acceptability of the study design for people living with incontinence and family members/significant others from all six study sites will be explored in interviews. A purposive sample of at least eight people living with incontinence who have capacity to consent and participate, from each of the three study sites that delivered the IAD manual will be invited to take part in individual or paired (with their family member/significant other) interview to understand their views of receiving care based on the IAD manual. Personal or nominated consultees of care home residents and adults living at home who lack capacity to consent will also be invited to participate in the interviews, so that these participants are not unfairly excluded. A purposive sample of at least eight care staff from each of the intervention sites will also be invited to participate in a focus group or an individual interview if they are unable to attend the focus groups. This is to explore if the intervention was used as intended, how it worked or did not work in practice, adherence to the IAD manual, and its acceptability among those delivering care. All interviews (or focus groups) will take place at the end of the 6-month feasibility trial. Staff participants will be purposively sampled for interview to reflect a range of genders and care roles, identified IAD champions and length of experience. See onlinesupplemental files 1^ 2^.

Care recipients will be purposively sampled to ensure interviews and observations of the IAD manual use take place across a range of participants to reflect a range of different (1) genders; (2) ages; (3) skin tones; (4) BMI (under/overweight/obese); (5) with IAD or intact skin; (6) with urinary incontinence, faecal incontinence or both.

